## Interventional methods

### Intervention group

Patients randomized to the exercise intervention group will follow a 6-month long progressive exercise training program. The program consists out of 6 weeks of MCT, followed by 20 weeks of MCT combined with HIIT. This 6-month period is followed by a maintenance, non-supervised, home-based physical activity program (Figure 2). During the first 6 months patients will participate in 18 supervised center-based exercise sessions in adjunct to a remotely monitored and guided home-based exercise intervention. The number of supervised center-based sessions will gradually decrease over time to encourage self-management and empowerment: during the first and second month, patients will participate in one supervised training session per week. Starting from the third month until the sixth, patients will participate in one supervised session every second week.

**FIGURE 2 F2:**
[figure not shown]
Overview of the training sessions in the exercise intervention and control group.

The 6-month exercise program consists of three phases. Aerobic training is performed three times per week on a cycle ergometer. Phase one is a 6-week run-in period to acquaint patients with the exercise therapy and allow a gradual and progressive aerobic conditioning. During this phase, three sessions of MCT are performed. In phase two, one session of MCT will be replaced by a HIIT session. During phase three, patients will execute two sessions of HIIT and one session of MCT. Duration and intensity of the training sessions are specified within Table 1. Intensity of the training sessions is guided by heart rate monitoring, corresponding to a specific percentage of the VO_2_ reserve. VO_2_ reserve is defined as ((VO_2_max—VO_2_rest) x %)—VO_2_rest) (Swain and Leutholtz, 1997). Patients will monitor their exercise (intensity, duration, frequency) by means of a commercial wearable exercise tracker and will be asked to upload their training data to the accompanying platform. In addition, their self-reported rate of perceived exertion is collected in an individualized training log. The 6-month exercise intervention will be followed by a maintenance physical activity program tailored to the patients’ preferences during a 60-min face-to-face consultation. The last 6 months of exercise are not supervised nor further supported by the study team.

**TABLE 1 T1:** Exercise intervention.

	Phase 1 Week 1–6	Phase 2 Week 7–12	Phase 3 Week 13–26
Supervised session	Week 1–6: 1x/week	Week 7–10: 1x/week Week 11–12: 1x/2 weeks	Week 13–26: 1x/2 weeks
Modality/week	3 x MCT	2 x MCT +1 x HIIT	1 x MCT +2 x HIIT
Warm-up	5 min, ramp to 25% VO_2_reserve	5 min, ramp to 25% VO_2_reserve	5 min, ramp to 25% VO_2_reserve
Duration (conditioning phase)	Week 1: 30 min	MCT: 45 min HIIT: 30 min [(6 × 2 min)+(6 × 3 min)]	MCT: 45 min HIIT: 28 min [(4 × 4 min)+(4 × 3 min)]
	Week 2: 35 min		
	Week 3: 35 min		
	Week 4: 35 min		
	Week 5: 40 min		
	Week 6: 45 min		
Intensity (conditioning phase)	Week 1–2: 50% VO_2_reserve Week 3–6: 65% VO_2_reserve	MCT	MCT
		65% VO_2_reserve	65% VO_2_reserve
		HIIT	HIIT
		6 × 2 min	4 × 4 min
		1 min ramp until 80% VO_2_reserve followed by 1 min sustaining 80% VO_2_reserve	1 min ramp until 85% VO_2_reserve followed by 3 min sustaining 85% VO_2_reserve
		Interspersed by 6 × 3 min	Interspersed by 4 × 3 min
		50% VO_2_reserve	60% VO_2_reserve
Cool down	5 min	5 min	5 min

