#### Exercise capacity testing

Cardiopulmonary exercise testing (CPET): Exercise capacity will be assessed by CPET to measure peak exercise oxygen consumption (VO_2_peak). CPET is performed on an electromagnetically braked cycle ergometer (Ergoline 900, Bitz, Germany) according to the standards of the American Thoracic Society/American College of Chest Physicians’ statement on cardiopulmonary exercise testing (American Thoracic SocietyAmerican College of Chest Physicians, 2003). Individualized ramp protocol will be performed until volitional exhaustion or appearance of clinically significant symptoms. Heart rate is continuously monitored using a 12-lead ECG. Respiratory data is continuously measured using breath-by-breath analysis (Oxycon Pro, Jaeger, CareFusion, Germany | JAEGER Vyntus CPX, Vyaire medical, United States). VO_2_peak is defined as the highest 30-s average of VO_2_ at the end of the test.

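### The printed expression for VO2 reserve subtracts resting uptake twice and cannot be the scale behind the 25–85% intensity labels in Table 1

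*Protocol article*

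**What the plan says.** Under Interventional methods, Intervention group, the text after Figure 2 explains how intensity is set: "Intensity of the training sessions is guided by heart rate monitoring, corresponding to a specific percentage of the VO_2_ reserve". The next sentence gives the rule: "VO_2_ reserve is defined as ((VO_2_max—VO_2_rest) x %)—VO_2_rest". In the article a further closing bracket follows, so the expression has two opening and three closing brackets.

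Table 1 then labels each part of the programme on this scale:

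- Warm-up, all phases: "5 min, ramp to 25% VO_2_reserve".
- Phase 1 moderate continuous training: "Week 1–2: 50% VO_2_reserve Week 3–6: 65% VO_2_reserve".
- Phase 2 high-intensity intervals: "1 min ramp until 80% VO_2_reserve followed by 1 min sustaining 80% VO_2_reserve", with 50% between intervals.
- Phase 3 high-intensity intervals: "1 min ramp until 85% VO_2_reserve followed by 3 min sustaining 85% VO_2_reserve", with 60% between intervals.

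The article gives no value for VO2max or VO2rest and no worked target. Exercise capacity testing says only how the peak is measured: "VO_2_peak is defined as the highest 30-s average of VO_2_ at the end of the test".

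**The concern.** A percentage of reserve should run from rest at 0% to maximum at 100%. The printed expression does neither. It also offers as the definition of the reserve something that already contains the percentage, while Table 1 goes on to prescribe percentages of that reserve.

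This is the only rule the article states for turning the Table 1 labels into targets. Heart-rate guidance does not bypass it, because the heart rate is said to correspond to a percentage of that same reserve. If the rule were applied as printed, the delivered intensity would fall below the label in every phase. If the two centres resolved the ambiguity differently, the intervention would differ by centre.

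Most sessions depend on the issued target. Three sessions a week for 26 weeks make 78. If the 18 supervised sessions count among them, 78 − 18 = 60 are done without on-site supervision. Controls are themselves advised to be active at moderate to high intensity, so the intensity reached in the exercise arm matters to the contrast under test.

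**Working it through.** **Inputs.** From the article: the printed expression and the Table 1 labels (p = 0.25, 0.50, 0.60, 0.65, 0.80, 0.85). Assumed, because the article gives no values: VO2rest 3.5 mL/kg/min and VO2max 20 to 35 mL/kg/min.

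**Notation.** R = VO2max − VO2rest, and k = VO2max / VO2rest. The printed expression is T = p × R − VO2rest.

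**Checks that need no assumed value.**

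- p = 0: T = −VO2rest, a negative oxygen uptake.
- p = 1: T = VO2max − VO2rest − VO2rest = VO2max − 2 × VO2rest.

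**Share of the reserve actually reached.** The expression can be read in two ways.

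- Reading A, T is a target VO2: share = (T − VO2rest) / R = p − 2/(k − 1).
- Reading B, T is an amount above rest: share = T / R = p − 1/(k − 1).

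Under both readings the share is below p whenever VO2rest is positive, so neither returns the label.

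**The 85% label with VO2rest 3.5.**

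| VO2max | R | T = 0.85R − 3.5 | Reading A: (T − 3.5)/R | Reading B: T/R |
|---|---|---|---|---|
| 20 | 16.5 | 10.525 | 42.6% | 63.8% |
| 25 | 21.5 | 14.775 | 52.4% | 68.7% |
| 30 | 26.5 | 19.025 | 58.6% | 71.8% |
| 35 | 31.5 | 23.275 | 62.8% | 73.9% |

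**Other labels at VO2max 25, VO2rest 3.5, reading A.** The shortfall is 7/21.5 = 32.6 percentage points at every label. So 80% becomes 47.4%, 65% becomes 32.4%, 60% becomes 27.4% and 50% becomes 17.4%.

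**Warm-up label, reading A.** T is below rest when 0.25R < 2 × VO2rest, that is k < 9, and negative when k < 5. At 25 and 3.5, T = 0.25 × 21.5 − 3.5 = 1.9 mL/kg/min, which is below the resting value.

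**Sensitivity to the assumptions.** Under reading A, the share at the 85% label runs from 12% to 69% across VO2max 15–40 and VO2rest 3–4 mL/kg/min.

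**Rest of Table 1.** The interval durations add up: 6 × 2 + 6 × 3 = 30 min and 4 × 4 + 4 × 3 = 28 min. The fault is confined to the expression and its relation to the labels.

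**The case against.** The strongest reply is that this is a misprint in a condensed article. The brackets do not balance, the same long dash appears at both places, and a source is cited for the concept. One wrong operator would be enough to explain the disagreement, and a typesetting or text-conversion fault cannot be excluded. No prescription sheet, worked target or conversion step shows the expression in use, and exercise tests with continuous ECG and gas data give each centre what it needs to set heart rates properly. Literal use would also tend to expose itself, since a warm-up target below resting uptake is hard to miss. Finally, Table 1 holds only percentage labels, so no tabulated VO2 or heart-rate value is contradicted.

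Most of this stands. It makes the harm conditional and lowers the urgency. It does not remove the error: the article chose to print a rule, and the rule cannot yield the labels it is meant to explain.

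A reader might go further and infer that sessions labelled 85% would be set at roughly half of the reserve. The article does not support that. It needs reading A and, for a share of 45–55%, a VO2max of about 21–27 mL/kg/min at VO2rest 3.5. Neither is stated, and reading B gives 64–74% for VO2max 20–35. Nor does anything in the article suggest that the two centres compute targets differently.

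**Conclusion.** The expression is wrong as printed and irreconcilable with the Table 1 labels for any positive VO2rest. That part rests on algebra alone and is certain.

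The size is not fixed by the article. With VO2rest 3.5 and VO2max 20–35 mL/kg/min assumed, literal use would place the 85% label at about 43–63% of the reserve (target VO2) or 64–74% (amount above rest). Whether any participant's target was affected cannot be known from the document. The point concerns how the intervention is specified. The sample size, power and significance level stated in the article do not depend on it. It is a correction worth making, but there is no evidence that training was delivered at the wrong intensity.

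**What to change.** Reconcile the expression in the Intervention group section with the percentage labels in Table 1, balance the brackets, and state whether the result is a target VO2 or an amount above rest. Which expression is intended is for the sponsor to say. Have both centres confirm that their heart-rate targets come from the same reconciled expression. If either centre finds that it used the printed form, the targets already issued there should be checked. The cost is a one-line correction and a short confirmation from two centres. No change to the design, sample size or analysis is needed.

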### Control group

The CG will verbally receive an exercise recommendation that is in line with current guidelines (Pelliccia et al., 2020). We will recommend physical activity of at least 150 min per week at a moderate to high intensity. No counselling or guidance on objective measures of physical activity by means of wearables will be provided.

### Concomitant care

Both intervention and control group will continue to receive all routine medical and pharmacological management.

### Assessments

An overview of all methods applied and a timetable of the scheduled visits is given in Table 2. The following section offers a summary of the diagnostic methods.

**TABLE 2 T2:** Examination overview for each visit.

Overview of examinations*	T0	T1	T2	T3	T4
Glaucoma Standard of Care					
Visual Acuity	X		X	X	X
Autorefraction/autokeratometry	X		X	X	X
Visual Field	X		X	X	X
Intraocular Pressure	X		X	X	X
Retinal Photography	X		X	X	X
Optical Coherence Tomography	X		X	X	X
Retinal Microvascular Assessments					
Static Retinal Vessel Analysis	X	X	X	X	
Dynamic Retinal Vessel Analysis	X	X	X	X	
Laser Speckle Flowgraphy (Basel)	X	X	X	X	
Optical Coherence Tomography Angiography	X	X	X	X	
Large Artery Structure and Function					
Flow Mediated Dilation	X	X	X	X	
Pulse Wave Velocity	X	X	X	X	
Physical Activity and Fitness					
Cardiopulmonary Exercise Testing (VO_2_peak)	X	X	X	X	
Accelerometer	X	X	X	X	
Further Assessments					
Anthropometry (Weight, Height, BMI, BP, ECG)	X	X	X	X	
24 h Ambulatory Blood Pressure Measurement	X	X	X	X	
Blood and Urine Sampling	X	X	X	X	
*Safety Monitoring*	*X*	*X*	*X*	*X*	
Questionnaires					
International Physical Activity Questionnaire (iPAQ)	X	X	X	X	
National Eye Institute 25-Item Visual Function Questionnaire (NEI VFQ-25)	X	X	X	X	
Glaucoma Activity Limitation questionnaire (GAL-9)	X	X	X	X	
Ocular Surface Disease Index (OSDI)	X	X	X	X	
Five-item Dry Eye Questionnaire (DEQ-5)	X	X	X	X	

T0, baseline; T1, measurement at 3 months; T2, measurement at 6 months; T3, measurement at 1 year; T4, yearly until 16 years; BMI, body mass index; BP, blood pressure; ECG, electrocardiography. *Safety will be monitored throughout the whole trial.

#### Clinical ophthalmological assessments

Visual field examination: Visual Field quantification is the gold standard for assessment of visual performance in glaucoma patients and are quintessential for glaucoma diagnosis and follow-up. The Humphrey visual field (Carl Zeiss Meditec, Inc., Dublin, CA) and Octopus visual field (Haag-Streit AG, Koeniz, Switzerland) are used for the examination.

Optical coherence tomography (OCT): OCT makes use of interferometry in the visible wavelength spectrum to make orthogonal slices of the retina in high resolution. Scanning of the macular retinal thickness (ganglion cell layer), retinal nerve fiber layer thickness and optic nerve rim assessment will be performed using Heidelberg Spectralis (Heidelberg Engineering Inc., Franklin, United States). In particular, a macular OCT cube as well as radial and circumpapillary scans across the ONH will be taken.

Optical coherence tomography angiography (OCTA): OCTA imaging can be best compared to subtraction angiography. It subtracts OCT images from each other, in which the only mobile part is the moving blood column. The result is a three-dimensional reconstruction of the retinal vascular tree to the level of the smallest capillaries. 10° and 20° vascular scans of the macula and 15° scans of the optic nerve will be captured using Heidelberg Spectralis (Heidelberg Engineering Inc., Franklin, United States).

Visual acuity testing: Visual acuity will be measured using a center-specific calibrated visual acuity chart and expressed in the universal Logarithm of the Minimum Angle of Resolution (LogMar) scoring.

Autorefraction/autokeratometry: The refraction (sphere, cylinder and axis) will be measured using an automated keratorefractometer. The optical qualities (refraction) of the eye are important for visual acuity testing and optical adjustment of imaging.

Intraocular pressure (IOP): IOP is measured by use of Goldmann Applanation Tonometry prior to pupil dilation.

#### Retinal microvascular assessments

Dynamic retinal vessel analysis: aFID and vFID are assessed as biomarkers of endothelial function of the retinal microcirculation. The dilation in response to flicker light is facilitated by neurovascular coupling. Dilation capacity in percent change from the baseline diameter will be assessed with the Dynamic Vessel Analyzer 3.0 (DVA, IMEDOS Systems, Jena, Germany) (Hanssen et al., 2022). The device consists of a retinal camera (Imedos Systems, Jena, Germany), a charge-coupled device camera for electronic online imaging and a personal computer for system control, analysis, and recording of the obtained data. Three cycles of flicker provocation are applied with 80 s of recovery after each of the cycle to extract a.o. the mean value for aFID and vFID (Streese et al., 2021).

Static retinal vessel analysis: Taking a fundus image of the retina allows for the assessment of CRAE and CRVE diameters as well as AVR. These parameters have been shown to reflect systemic CV risk when analyzed in the healthy eye and represent retinal microvascular health (Hanssen et al., 2022). Retinal vessel images will be taken using the Static Retinal Vessel Analyzer (SVA-T, Imedos Systems UG, Jena, Germany). The SVA-T system consists out of a fundus camera (Topcon TRC NW8) and analyzing software (Visualis 2.80, Imedos System UG). Three images will be taken from the retina of the affected eye. Retinal vessel diameters will be identified and analyzed by use of a semi-automated software (Vesselmap 2, Visualis, Imedos Systems UG) and automated softwares (LUNet and PVBM) (Fhima et al., 2023).

Laser speckle flowgraphy (LSFG): The ocular perfusion will be measured with laser flowgraphy (mean blur rate, MBR, as estimate for flow) with LSFG (Nidek Inc., United States) only at the Basel site. The device uses a low-power semi-conductor laser (wavelength of 830 nm, laser class 1) for its measurement light. LSFG measures real-time fundus blood flow. The relative blood flow is expressed as an arbitrary unit of MBR. A total of 118 frames will be recorded for 4 s. Mean perfusion in the ONH will be analyzed with LSFG Analyzer software (version: 1.0.0.0).

#### Macrovascular assessments

Flow-mediated dilation: FMD is the gold standard method for non-invasive evaluation of endothelial function in large arteries. Using an ultrasound-based device (2D imaging), dilation of the brachial artery is measured for 3 minutes after 5 minutes of cuff-induced blood flow restriction (UNEX Sakae Nakaku Nagoya; Japan). The diameter of the brachial artery is measured at rest (rest diameter), shortly before cuff deflation (base diameter) and during 3 minutes of increased blood flow (max diameter) to analyze flow and endothelium-dependent vasodilation. Blunted FMD has been linked to higher CV event risk and it has been shown to have a prognostic value for development of CVD (Ras et al., 2013).

Pulse-wave velocity and analysis: Carotid-femoral pulse wave velocity and estimates of the central aortic blood pressure will be measured using the SphygmoCor XCEL (Atcor Medical, [name], Naperville, United States). PWV is the gold standard for the measurement of arterial stiffness (Chalmers et al., 2010). A good intra- and interobserver reproducibility of this technique has been demonstrated in healthy populations and in patients with elevated CV risk (Streese et al., 2020b). After 10 minutes of rest, pulse waves are recorded using a high-fidelity tonometric transducer at the carotid site with simultaneous recording of pulse waves using a cuff-based oscillometric detection at the upper leg. Pulse wave distance is determined by use of the direct method, as recommended in a previous consensus document (Van Bortel et al., 2012). The distance from the carotid artery to the top of the cuff is measured, followed by the distance from the femoral artery to the top of the cuff. Distance between the carotid and femoral palpation site is calculated via subtraction. The measurements meet quality control parameters if three consecutive measurements are visually acceptable and within 0.5 m/s of each other with a standard deviation of <10%. The mean of all valid measurements represents the PWV value.

#### Exercise capacity testing

Cardiopulmonary exercise testing (CPET): Exercise capacity will be assessed by CPET to measure peak exercise oxygen consumption (VO_2_peak). CPET is performed on an electromagnetically braked cycle ergometer (Ergoline 900, Bitz, Germany) according to the standards of the American Thoracic Society/American College of Chest Physicians’ statement on cardiopulmonary exercise testing (American Thoracic SocietyAmerican College of Chest Physicians, 2003). Individualized ramp protocol will be performed until volitional exhaustion or appearance of clinically significant symptoms. Heart rate is continuously monitored using a 12-lead ECG. Respiratory data is continuously measured using breath-by-breath analysis (Oxycon Pro, Jaeger, CareFusion, Germany | JAEGER Vyntus CPX, Vyaire medical, United States). VO_2_peak is defined as the highest 30-s average of VO_2_ at the end of the test.

### Blood and urine sampling

Blood will be drawn in a fasted state by venipuncture of the cubital fossa for both routine analysis as well as circulating biomarkers of systemic CV risk, after at least 1 day of rest after the last physical exercise but within 1 week. This will be performed at baseline, after 3 months, 6 months and 12 months of trial inclusion. Urine will also be collected in a fastened state. Routine urine analysis will be used for the determination of microalbuminuria. Routine blood analyses encompass:• Hemogram with differential blood cell count.• Biochemistry: high-sensitive c-reactive protein (hsCRP), glucose, HDL, LDL, triglicerides, HbA1c, kidney markers (creatinine, sodium, potassium).• Biomarkers of endothelial function and premature vascular ageing comprise different cellular (circulating mature endothelial and endothelial progenitor cells; only assessed in Basel) and protein markers, but also transcriptomics, genomics and epigenetic markers.• ELISA kits will be used according to the manufacturers’ instructions for the determination of interleukine-6 (Bender Med-Systems, Austria), tumor necrosis factor-α (Biosource, United States), 3-nitrotyrosine (oxidative stress, Cell Biolabs, CA, United States), and BDNF (Biosensis, United States). High-sensitive c-reactive protein (hs-CRP) is analysed by immunoturbidimetric latex CRP assay (Cobas 8000, Roche-Diagnostics, Basel).

Blood samples are centrifuged, and the supernatant aliquots are frozen at −80°C for batch analysis.

#### Questionnaires

International Physical Activity Questionnaire (iPAQ): The short form of the iPAQ is used in the validated German and Dutch versions. It is applied to identify the quantity and kind of daily physical activity in all participants. From the questionnaire, the metabolic equivalents (MET) per 1 hour (met/h) can be calculated per week. The instrument has demonstrated good reliability and validity (Craig et al., 2003).

National Eye Institute 25-Item Visual Function Questionnaire (NEI VFQ-25): NEI VFQ-25 assesses vision related quality of life (vision comfort in daily activities as driving, newspaper reading and cinema) (Mangione et al., 2001).

Glaucoma Activity Limitation Questionnaire (GAL-9): GAL-9 is the shortened version of the Glaucoma Quality of Life-15 and also assesses vision related quality of life, specifically developed for glaucoma patients (Nayyar et al., 2022).

Ocular Surface Disease Index (OSDI): OSDI assesses the effects of dry eye disease on vision-related function (Guarnieri et al., 2020).

Five-item Dry Eye Questionnaire (DEQ-5): DEQ-5 will be used to discriminate self-assessed severity of dry eye disease (Chalmers et al., 2010).

#### Further assessments

Daily physical activity: physical activity at baseline, three and 6 months as well as 12 months of follow-up will be measured objectively through a validated research-based accelerometer (GENEActiv ActiGraph™ GT3X, ActiGraph LLC, Pensacola, Florida, United States), that will be worn for 8 consecutive days in order to obtain number of steps, energy expenditure, MET rates, physical activity intensity, sedentary bouts, activity counts and activity bouts.

24 h ambulatory blood pressure measurement: Patients will receive a validated oscillometric (either 90202 or 90207 SpaceLabs monitor (SpaceLabs Inc., Redmond, WA) or ABPMpro—Research model (SOMNOmedics GmbH, Randersacker, GER)) which will be programmed to obtain ambulatory blood pressure readings at intervals of 15 or 20 min during the day (from 06:00 to 00:00) and at 30-min intervals during the night (from 00:00 to 06:00).

Anthropometry: Patient’s height, weight, body mass index (BMI), resting electrocardiogram (ECG), and blood pressure (BP) will all be measured using standardized procedures. Body fat will be measured with bioelectrical impedance analysis (InBody, Biospace, California, United States).

